## Abstract

*Background*. Cancer-related fatigue (CRF) is a painful, persistent feeling of physical and cognitive subjective fatigue related to cancer or cancer remedy. The occurrence of CRF may be related to the hypothalamic-pituitary-adrenaline (HPA) axis, inflammatory mediator theory, and gut microbiota. Moreover, acupuncture could play a vital part in the therapy of CRF. The study will evaluate whether acupuncture can improve fatigue symptoms of CRF patients after breast cancer chemotherapy by regulating the gut-brain axis. *Methods/design*. Seventy patients with CRF will be enrolled in this study, with 35 patients randomly assigned to each group. Blood and feces will be collected at the beginning and end of treatment. Piper fatigue scale, KPS score scale, and quality-of-life scale will be used to observe the changes of fatigue symptoms and life quality of CRF patients and to evaluate the effect of acupuncture on CRF. Then, the method of ELISA will be used to explore the regulatory effect of acupuncture on the HPA axis and inflammatory cytokines. Moreover, based on 16SrDNA, the changes of gut microbiota structure and flora of CRF patients will be observed. Ultimately, the correlation analysis of gut microbiota can be related to inflammatory cytokines, HPA axis, and clinical efficacy evaluation. *Discussion*. This study will identify the effect and the mechanism of acupuncture therapy in CRF. And it will offer an alternative treatment modality for the treatment of CRF after chemotherapy for breast cancer. Furthermore, it will also provide the clinical and theoretical bases for the extensive application of acupuncture therapy in tumor rehabilitation. *Trial Status*. Protocol version number and date: V2.0, 6 May 2021. The trial is registered with the Chinese Clinical Trial Registry on 20 June 2021 (trial identifier: ChiCTR2100047510).

## 1. Introduction

Breast cancer is one of the most common malignancies among women in the world, according to the latest global cancer data in 2020 released by the World Health Organization International Agency for Research on Cancer (IARC); the incidence of breast cancer ranks first in the world [1–3]. With the development of breast cancer research and advanced treatment techniques and monitoring methods, the survival time of people with breast cancer was remarkably prolonged. Nevertheless, on account of the cancer illness and treatment process, the majority of breast cancer survivors have a variety of physical and psychological reactions, such as sleep disorders, cancer-related fatigue, and depression [4]. A large number of patients with breast cancer suffered different degrees of tiredness several months after diagnosis. In particular, nearly half of the patients still experienced severe CRF postdiagnosis [5, 6]. The National Comprehensive Cancer Network (NCCN) defines cancer-related fatigue (CRF) as a persistent subjective sensation caused by cancer or cancer remedy that disrupts normal bodily function and seriously affects the patient's physical function and quality of life. In addition, the incidence of CRF occurs in 70% to 100% of cancer patients who receive chemotherapy [7, 8].

For the past few years, many studies have found that the incidence rate of CRF may be connected to the hypothalamic-pituitary-adrenaline (HPA) axis, inflammatory mediator theory, and gut microbiota [9]. The researchers demonstrated that both the tumor and its treatment could activate the proinflammatory cytokine network [10]. At the same time, these inflammatory factors enter the brain in various ways. Then, these factors disrupt the HPA axis, reduce the synthesis and release of cortisol, and ultimately cause fatigue [11]. Moreover, inflammatory cytokines can be used as an indicator of immune function in patients with CRF [12]. Besides, the gut microbiota is involved in the development of CRF, and it can directly influence immune system cytokines, corticotropin-releasing hormone and cortisol (CORT), thereby affecting the HPA axis and brain function [13, 14].

Nonpharmacological treatment of CRF includes exercise, psychological intervention, health education, CBT, sleep improvement, and nutrition counseling. Moreover, drug intervention mainly includes central stimulants. But these measures mostly belong to the symptomatic treatment; the overall effect is not satisfactory.

Given this, we are actively exploring new approaches. Abundant studies have found that traditional Chinese medicine plays a vital part in the therapy of CRF. In particular, acupuncture has the advantages of dredging the channels and collaterals, regulating the viscera, running qi and blood, strengthening the body, and dispelling the harmful factors. In the recent study, it is clear that acupuncture can regulate the changes of CORT and adrenocorticotrophic hormone (ACTH) levels in the HPA axis by affecting the changes of gut microbiota and inhibiting the activation of inflammatory cytokines, and ultimately reduce the level of cancer-related fatigue in patients. This way provides a theoretical basis for the extensive application of traditional acupuncture in tumor rehabilitation. Meanwhile, it has the advantages of low cost, short time consumption, and fewer side effects. Therefore, the study designed a randomized controlled trial comparing acupuncture and rehabilitation exercise to observe the clinical efficacy of acupuncture in the treatment of CRF patients with breast cancer after chemotherapy. Our purpose is to gain further results through laboratory examinations and scale assessments. These results will help to demonstrate whether acupuncture can improve CRF as an effective new treatment method in these patients.

## 2. Objectives

To observe the treatment of acupuncture in improving CRF with breast cancer after chemotherapy in patientsTo clarify that the acupuncture affects the expression level of inflammatory cytokines in the immune system by regulating the structural changes of intestinal flora, then regulates the changes of HPA axis function, and finally plays a role in improving fatigue symptoms

## 3. Design and Methods

### 3.1. Trial Design and Setting

This is a randomized controlled study to explore whether acupuncture can improve fatigue symptoms of CRF patients after breast cancer chemotherapy by regulating the gut-brain axis. Seventy participants will be randomly assigned to either the acupuncture group or the primary treatment group with 35 patients in each group in a 1 : 1 ratio. Relevant tests will be tested on both groups at the baseline and after 3 weeks of the treatment. Blood and feces will be collected at the beginning and end of treatment. Piper fatigue scale, KPS score scale, and quality-of-life scale will be used to observe the changes in fatigue symptoms and quality of life of CRF patients in two groups before and after treatment and to inspect the curative effect of acupuncture on CRF. Then, the method of ELISA will be used to explore the regulatory effect of acupuncture on the HPA axis and inflammatory cytokines. Moreover, based on 16SrDNA technology, the changes in gut microbiota structure and flora of CRF patients will be observed. Ultimately, the correlation analysis of gut microbiota content can be related to inflammatory cytokines, HPA axis, and clinical efficacy evaluation (Figure 1 and Table 1).

### 3.2. Participants

The participants with breast cancer after chemotherapy who suffer from fatigue according to the diagnostic criteria of CRF will be collected from the First Affiliated Hospital of Henan University of Chinese Medicine. All participants will be assessed with various tests and scales at the baseline. If the patients meet the inclusion criteria, they will sign the informed consent to prepare for the next trial.

### 3.3. Eligibility Criteria

#### 3.3.1. Inclusion Criteria

Inclusion criteria require that the participants (1) match the diagnosis of having CRF according to the diagnostic criteria of ICD-10 for CRF; (2) with breast cancer will be diagnosed by pathology or cytology; (3) must be between 18 and 80 years; (4) must have a KPS score above 50 and have an expected survival time of half a year or more; (5) have previously undergone chemotherapy, and they will have no other treatment plan for the next 21 days; (6) have no mental disorder or cognitive impairment and have normal language expression ability and can understand the scale content and cooperate with treatment; (7) have no serious heart, liver, or kidney diseases; and (8) have signed a written informed consent form.

#### 3.3.2. Exclusion Criteria

Participants will be excluded if they (1) have severe systemic diseases, such as cardiovascular disease, acute infectious disease, liver or kidney diseases; (2) have mental or psychological diseases with definite diagnosis, including cognitive impairment, anxiety, and depression syndrome; (3) are pregnant and breastfeeding; (4) are allergic to alcohol and needles or afraid of the acupuncture; (5) have a language communication disorder or other reasons cannot allow them to cooperate with follow-up and examination; and (6) have another clinical trial during enrolment.

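### Eligibility screens for tolerance of acupuncture but not of the jogging control, so patients suited to only one arm can be randomised

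*Protocol article*

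**What the plan says.** Sections 3.3.1 and 3.3.2 of the Protocol article list 8 inclusion and 6 exclusion items. Exclusion 4 applies to patients who "are allergic to alcohol and needles or afraid of the acupuncture". It screens both medical tolerance and willingness, and only for needling.

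The control (section 3.6) is jogging for 30 minutes, five times a week for three weeks, with heart rate held at half of an age-predicted maximum. No listed item refers to exercise.

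The general items that bear on it apply to both arms:

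- The patient "must have a KPS score above 50 and have an expected survival time of half a year or more". Section 3.7 classes KPS 50 to 70 as semi-independent.
- The patient "must be between 18 and 80 years".
- The patient "can understand the scale content and cooperate with treatment".
- Patients must "have no serious heart, liver, or kidney diseases", and are excluded if they "have severe systemic diseases, such as cardiovascular disease, acute infectious disease, liver or kidney diseases".
- Patients must "have signed a written informed consent form".

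Section 3.9 also requires physical examination and vital signs before, during and after treatment. Table 1 puts the eligibility screen at week -1 and randomisation at week 0.

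**The concern.** Randomisation makes the arms comparable among patients who could receive either treatment. Here a patient can pass every listed item and be fit for needling but not for jogging. Allocated to acupuncture, that patient is treated as planned. Allocated to control, the same patient may withdraw, remain untreated or be exposed to avoidable risk.

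Loss or non-delivery can then differ between arms because of the arm itself, and randomisation does not protect against that. The single 15% dropout allowance in section 3.5 covers the number lost, not an imbalance in who is lost.

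The population makes the situation plausible: everyone enrolled has fatigue after chemotherapy, age runs to 80, and KPS 60 is admissible. Section 3.4 has participants unaware of their group when treatment starts, so reluctance to jog may appear only after allocation.

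**Working it through.** **The plan's own figure.** Section 3.5 gives means of 5.17 (SD 1.26, control) and 4.17 (SD 1.14, acupuncture), two-sided alpha 0.05 and power 0.90. The difference is 1.00 and the average SD is √[(1.26² + 1.14²)/2] = 1.20. The normal approximation gives 31 per group and the t-test 31.3, so 32; the plan states 30. Inflating 30 for 15% gives 30 × 1.15 = 34.5, so 35 as stated (30/0.85 = 35.3 would give 36). The plan's figures reproduce to within two patients and are used below.

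**The control prescription.** Sessions: 5 × 3 = 15. Heart-rate cap: 0.5 × (220 − age), which is 85 bpm at age 50 and 70 bpm at age 80.

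**Bias, all inputs assumed.** Let k of 35 patients per arm be unable or unwilling to exercise, with f = k/35. Let d be how much worse they score than the others, and b the exercise benefit they forgo; both are taken as 0.5 to 1.0 point.

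- *Removed from control only:* the control mean falls by f × d, which works against acupuncture.
- *Removed from control, and half as many removed from acupuncture:* the net shift is d × (f/2)/(1 − f/2), also against acupuncture.
- *Equal loss in both arms:* the shift is 0.
- *Kept in the control group without exercising:* the control mean rises by f × b, which favours acupuncture.

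| k of 35 | f | Removed, control only (f × d) | Half that loss in acupuncture | Kept, unexercised (f × b) |
|---|---|---|---|---|
| 4 | 0.114 | 0.06 to 0.11 against | 0.03 to 0.06 against | 0.06 to 0.11 in favour |
| 7 | 0.200 | 0.10 to 0.20 against | 0.06 to 0.11 against | 0.10 to 0.20 in favour |
| 10 | 0.286 | 0.14 to 0.29 against | 0.08 to 0.17 against | 0.14 to 0.29 in favour |

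The assumed range is −0.29 to +0.29 around the planned 1.00.

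**Power.** This uses a two-sided pooled t-test with difference 1.00, the SDs above and 30 patients in acupuncture. The plan already lets 35 fall to 30, a loss of 5 (5/35 = 14%).

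| Controls analysed | How reached | Power |
|---|---|---|
| 30 | planned loss of 5 | 0.887 |
| 28 | total loss of 7 | 0.877 |
| 25 | total loss of 10 | 0.858 |
| 26 | 4 on top of the planned 5 | 0.865 |
| 23 | 7 on top of the planned 5 | 0.843 |
| 20 | 10 on top of the planned 5 | 0.815 |

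A total loss of 4 lies inside the allowance. The pooled SD here is weighted by group size. Using the unweighted average SD of 1.20 lowers some entries slightly (for example 0.875 at 28 and 0.855 at 25) and changes nothing in the reading.

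**The case against.** The best counter-argument is that an arm-neutral item already exists: inclusion 6 requires that the patient "can understand the scale content and cooperate with treatment", and in a two-arm trial treatment can be read as either arm. The cardiac and systemic exclusions, the KPS floor, the low age-adjusted heart-rate cap, the examinations and consent add cover. Exercise is also a recognised option in this population; the Introduction says "Nonpharmacological treatment of CRF includes exercise". Eligibility lists need not mirror each other arm by arm, and a condensed article may omit operational screening. Every rate used above is assumed, the sign of the effect is open, and if patients are analysed as randomised, non-adherence is part of comparing the assigned strategies.

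Much of this stands. The safeguards are real and leave a narrow gap, the lists are asymmetric rather than contradictory, and the size is unknown.

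It does not close the gap. The cooperation wording sits in an item about mental state, language and understanding the scales, so a screener would not naturally read it as fitness to jog. The organ-disease items do not reach joint, gait, skeletal or frailty limits. The heart-rate cap limits cardiac load, but the prescribed activity is still jogging. The section 3.9 examinations are not tied to any decision on eligibility for exercise. The criteria are given as full numbered lists in which an acupuncture-specific item was kept. Analysing everyone as randomised would avoid the removal bias but would neither deliver the control treatment nor remove the safety question.

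**Conclusion.** The concern holds. As written, a patient aged up to 80 at KPS 60 with a joint or gait limitation, and without severe systemic disease, is eligible and may be allocated to 15 jogging sessions. The consequence is possible imbalance between the arms in loss or treatment delivery, plus avoidable risk to some controls.

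Neither size nor direction can be determined from the document. The shift of up to 0.29 point either way is 29% of the planned difference, and it requires 10 of 35 controls to be affected with a full 1.0-point gap or lost benefit. With 4 of 35 it is at most 0.11. Power is a side issue, since it stays above 0.81 in every scenario considered. This is a design weakness that should be corrected because the correction is cheap. It does not by itself invalidate the comparison.

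**What to change.** Add one criterion that applies to both arms: in the investigator's judgement the patient is able, and the patient states willingness, to undergo either the acupuncture or the exercise programme, with no contraindication to either. Check it at the week -1 screen, before randomisation at week 0, and do not randomise anyone suited to only one arm. The investigators should decide which mobility, skeletal or frailty limits count. The KPS floor, sample size and analysis need not change.

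The cost is one criterion and one line at a screening visit that already exists, with slightly slower recruitment and a slightly fitter study population.

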### 3.5. Sample Size

According to the results of previous literature (clinical study on an acupuncture fatigue group for cancer-related fatigue of qi and blood deficiency type), the average fatigue scale score of the control group was 5.17 ± 1.26, and the average score of the fatigue scale in the acupuncture group was 4.17 ± 1.14. In our study, we will set the following parameters: *α* = 0.05, 2-sided, power = 0.9. Our software PASS (Version 15.0) will be used to calculate the sample size of the treatment group and the control group, and the result is 30 in each group. Considering the loss of sample size caused by the 15% dropout rate, the final calculation will require at least 35 cases in the treatment group and 35 cases in the control group, and a total of at least 70 cases will be included.

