### 3.6. Intervention

The different treatments will be performed for thirty-five participants in each group. They will have experienced it five times a week for three weeks in separate compartments. These therapists are experienced doctors who have obtained medical qualifications. Before the trial, they will receive training to ensure adherence to the study protocol. Meanwhile, each therapist will be kept ignorant of the group allocation. The various separate interventions in two groups are as follows.

In the treatment group, according to the relevant literature research, the most commonly used acupoints for the treatment of CRF were summarized, and Zusanli (ST36), Sanyinjiao (SP6), Qihai (CV6), Guanyuan (CV4), and Baihui (GV20) will be selected. The orientation of acupoints derives from the planning textbook of traditional Chinese medicine colleges and universities, *Acupuncture and Moxibustion Science*. First, in the study, the therapists will use the single-use sterile needles (Hwato, Suzhou, China) to puncture these patients. 40 mm long needles (0.35 mm in diameter) are used to puncture points on the limb and abdomen. 25 mm long needles (0.3 mm in diameter) are used for head points. All needles are manually manipulated by flat reinforcing and flat reducing methods to create the certain experience termed as De Qi that occurs in both the patients and therapists. Participants will receive five acupuncture sessions per week, and each session will last for 30 min. In the control group, participants will take on aerobic exercise through jogging mode, in which the heart rate will be controlled at 50% of the maximum heart rate (maximum heart rate = 220 − patient′s age). They will also receive five exercise sessions per week, and each session will last for 30 min.

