### 3.8. Other Outcome Measures

#### 3.8.1. The Expression of HPA Axis-Related Hormone Factors and Inflammatory Cytokines

Blood samples of CRF patients in the acupuncture group and the basic treatment group will be collected for testing before and 3 weeks after treatment, respectively. Fast-fasting blood samples will be collected from all subjects in the morning. And the collected samples will be centrifuged at 3000 rpm at 4°C for 15 min. Moreover, Serums will be collected and stored at -80°C. Human serum CORT, ACTH, IL-6, IL-1*β*, and TNF-*α* enzyme-linked immunosorbent assay kit will be used for detection. In addition, the ELISA kit will be balanced at room temperature for 30 min, and the samples will be dissolved at room temperature. Standard samples with different gradient concentrations will be prepared, and a standard diluent will be added. We will add 50 *μ*l of biotin-binding antibody to each well, seal the plates, place in a horizontal shaker to shake slightly and mix, and incubate at room temperature for 2.5 h. We will discard the supernatant, add the detection antibody, and incubate at room temperature for 1 h. We will discard the supernatant and incubate in the dark at room temperature. Then, we will add the stop solution and, after fully mixing, detect the absorbance OD value at 450 nm with the enzyme plate analyzer.

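### The numbered eligibility criteria do not clearly exclude a known bleeding disorder, therapeutic anticoagulation or known low platelets before a course of needling in patients who have had chemotherapy

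*Protocol article*

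**What the plan says.** Section 3.3.1 lists eight numbered inclusion criteria and section 3.3.2 six numbered exclusion criteria. The items that bear on this point are:

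- Exclusion (4), the only one written around needling: patients who "are allergic to alcohol and needles or afraid of the acupuncture".
- Exclusion (1): patients who "have severe systemic diseases, such as cardiovascular disease, acute infectious disease, liver or kidney diseases".
- Inclusion (7): patients must "have no serious heart, liver, or kidney diseases".
- Inclusion (5): patients must "have previously undergone chemotherapy, and they will have no other treatment plan for the next 21 days".

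Section 3.2 adds: "All participants will be assessed with various tests and scales at the baseline". It does not say which tests.

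Section 3.6 describes manual needling of limb and abdominal points with needles 40 mm long and 0.35 mm in diameter, and of the head point with 25 mm needles. On frequency it says: "Participants will receive five acupuncture sessions per week, and each session will last for 30 min". The course runs for three weeks. The control arm jogs and is not needled.

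Section 3.9 names hemorrhage and hematoma as possible after acupuncture, describes reactions as uncommon and mild, and expects bleeding to settle with pressure at the site. It requires physical examination and vital signs before, during and after treatment.

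**The concern.** The trial names bleeding as an effect of its intervention and recruits only patients who have had chemotherapy. Its entry criteria nevertheless screen for needle and alcohol allergy and for fear, and not for the conditions that make bleeding harder to stop. The advice in section 3.9 that bleeding resolves with pressure presumes adequate clotting, and no listed criterion clearly secures that.

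What is at stake is the safety of individual patients in the acupuncture arm, since only that arm carries the needling risk. The comparison of the arms is not at stake.

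**Working it through.** The plan states no figure on this point, so the check is a reading of each provision against three kinds of patient.

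**Count of items.** Inclusion 8 + exclusion 6 = 14. Items specific to needling: 1, exclusion (4). Items naming a bleeding disorder, anticoagulants or platelets: 0.

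**Exposure per patient.** 5 sessions a week × 3 weeks = 15 sessions.

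**Time since chemotherapy.** Inclusion (5) requires past chemotherapy and looks forward 21 days, which is the length of the course (3 × 7 = 21). Nothing looks back, so a patient a few days past a cycle meets it.

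**Which provisions reach which patients:**

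| Provision | Known bleeding disorder | Therapeutic anticoagulation | Known low platelets |
|---|---|---|---|
| Exclusion (1), severe systemic disease, open-ended list | Reached if judged severe | Reached if given for severe cardiovascular disease; otherwise not clearly | Not clearly, unless part of a severe illness |
| Inclusion (7), heart, liver, kidney | Not named | Reached if given for serious heart disease | Not named |
| Inclusion (5), treatment in the next 21 days | Not reached | Only on a broad reading of treatment; the context is chemotherapy | Not reached |
| Exclusion (4), allergy or fear | Not reached | Not reached | Not reached |
| Baseline tests, section 3.2 | Unspecified; no excluding result stated | Unspecified | A count can be neither assumed nor ruled out; no excluding result stated |
| Physical examination, section 3.9 | May show visible signs | May show visible signs | May show visible signs; measures no count |

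**Laboratory schedule.** Table 1 places the eligibility screen at Week -1 and its one blood item at Weeks 0 and 4. Section 3.8.1 describes only cortisol, ACTH, IL-6, IL-1β and TNF-α on that blood, for which an "enzyme-linked immunosorbent assay kit will be used for detection". No platelet count or clotting test is described.

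**Result.** Each kind of patient is reached in part, and none is clearly excluded. The gaps that remain are a bleeding disorder not judged severe, anticoagulation for a reason other than severe heart disease, and low platelets without severe illness.

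**The case against.** **This is a condensed article.** The full protocol, V2.0, is not shown and may hold further criteria or drug rules. That limits confidence. But the lists are numbered, are presented as the trial's criteria, and go down to alcohol allergy and fear. The point is confined to what they state. If the full protocol already has such an item, confirming it closes the matter.

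**Nothing in the text is contradictory, and no sentence says that needling is hazardous in these patients.** True. The step from impaired clotting to less reliable control of bleeding is ordinary clinical reasoning, stated here as an assumption.

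**Other safeguards exist.** The therapists are experienced, qualified doctors who could withhold needling, examinations continue during treatment, and adverse events are recorded from Week 1 to Week 4. These narrow the practical gap. They act after allocation, however, and adverse-event recording detects bleeding without preventing it.

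**Stronger readings that the document does not support:**

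- A reader might add low neutrophils to the gap. The needling harms named in section 3.9 are bleeding, not infection. Infection is already addressed by the exclusion of acute infectious disease, by single-use sterile needles and by disinfection.
- A reader might think that requiring a count dated after the last cycle would make up for the missing minimum interval. A count taken the next day would qualify and could miss a later fall, and requiring a new count could add a procedure.
- A reader might multiply 15 sessions by the size of the arm to size the problem. That gives total exposure, not sessions in patients at risk.
- A reader might take the Discussion's remark that acupuncture improves myelosuppression as reassurance. It does not say whether needling is safe at low counts.

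**Conclusion.** The point holds as a cheap patient-safety improvement. Of 14 numbered criteria, one is specific to needling and none clearly excludes a known bleeding disorder, current therapeutic anticoagulation or known low platelets. A site following the lists exactly could randomise such a patient to a course of 15 sessions.

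This rests on two assumptions: that the published lists are the operative criteria, and that pressure at the site is less dependable when clotting is impaired. The document gives no rate of bleeding, anticoagulant use or low platelets, so the number of patients affected cannot be stated and no harm rate is claimed. A reader might infer that the trial is unsafe as designed. The text does not support that, because partial safeguards exist and the expected reactions are described as mild. No estimate, test or sample size changes.

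**What to change.** Add one item to section 3.3.2: a known bleeding disorder, current therapeutic anticoagulation, or known clinically significant thrombocytopenia on the most recent available routine blood count. The investigators should fix the platelet cut-off before recruitment starts.

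Check it at the Week -1 screen from history and existing records. Apply it to both arms before randomisation so that the groups stay comparable, even though only one arm is needled.

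The item does not replace a minimum interval since chemotherapy and should not be presented as doing so.

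Cost: one line of text, a look at existing records, a few more screen failures and slightly slower recruitment. No new test is required, and the target of 70 patients stands.
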